### 2.4 The baseline and follow-up

In the baseline and the follow-up, five aspects of characteristics/variables will be collected: demographics, cancer-related information, exercise habits and lifestyle, health-related physical fitness (21), and CVD-related items. Table 1 illustrates these variables in detail.

**TABLE 1 T1:** Characteristics of participants in the baseline and at follow-up.

Category	Variables	Measurement/method	References
Demographics	Age	Electronic health record (EHR)	(22)
	Sex	EHR	(23)
	Marital status	Self-reported	(24)
	Education level	Self-reported	(25)
Cancer-related information	Cancer types	EHR	(26–31)
	Years living/diagnosed with cancer	EHR	
	Cancer treatment	EHR	
	Current medication (drugs used)	EHR	
Exercise habit and lifestyle	Smoking status	Self-reported	(32)
	Alcohol use	Self-reported	(33)
	Physical activity	IPAQ-L: International physical activity questionnaire (34)	(35)
	Diet	DHQ: diet history questionnaire (36)	(37)
	Sleep	PSQI: Pittsburgh sleep quality index (38)	(39)
Health-related physical fitness (21)	Body composition-anthropometry	Body mass index (BMI), body weight, height, muscle mass, fat mass, percentage of body fat, etc., by Inbody Device (40)	(41)
	Cardiorespiratory fitness (CRF)	Cooper 12 min run test (42)	(43)
	Muscle strength	Grips (44)	(45)
	Body flexibility	Sit-and-reach (46)	(47)
CVD-related items	Blood pressure	Medical test	(48)
	BPV: blood pressure variability	Medical test	(49)
	Resting heart rate	Medical test	(50)
	24-h ECG: premature beat, etc.	Medical test	(51)
	Echocardiography	Medical test	(52)
	Other relevant biochemical parameters	Medical test	(53)

Specifically, demographics, cancer-related information, exercise habits and lifestyle, and health-related physical fitness are used for exercise prescriptions, while CVD-related items are used to evaluate the effectiveness of exercise prescriptions after comparing them with the follow-up data.

### 2.5 Interventional methods

The interventional method for all participants is the exercise prescription, prescribed by our ACSM-CASM certificated exercise prescription doctors. The exercise intervention strategies are prescribed based on each participant’s baseline characteristics including demographics, cancer-related information, exercise habits and lifestyle, and health-related physical fitness.

From the professional perspective, exercise prescription doctors will determine the exercise dose considering three aspects: frequency, duration, and intensity (26). To be specific, doctors prescribe an exercise dose such as “3 times of exercise per week, 150 minutes in total, in moderate intensity” or “5 times of exercise per week, 75 minutes for each time, in high-intensity.” Frequency is the number of times of exercise per week, duration is the length of time in total, and intensity is decided to be high, moderate, or low. Furthermore, we can employ the concept of metabolic equivalent of task (MET) in exercise dose when considering frequency, duration, and intensity (54). For example, the above-mentioned two exercise doses are equivalent to each other, and both represent 7.5 MET-h/week.

During the 2-year exercise intervention period, wearable devices will be applied to monitor each participant’s completion status. In addition, our professional health management team (including certificated CEPs by ACSM-CASM programs and several assistants who hold a degree in public health, sports training, physical education, social work or psychology) will keep track of participants every week to ensure their adherence. The employment of wearable devices will be charged a deposit fee at the beginning which will be returned after the follow-up. Participants who are kept in track by our health management team during these 2 years will be given sports equipment (e.g., badminton rackets, yoga mats, foam rollers) for free every 6 months.

### 2.6 Data analysis and interpretable learning

Effective exercise prescriptions will be selected based on pre- and post-intervention data analysis of CVD-related items. For example, if the blood pressure variability decreases or at least does not increase, the exercise prescription can be considered effective. We will employ interpretable machine learning models to the learnings on exercise prescription recommendations for all effective prescriptions.

Demographics, cancer-related information, exercise habits and lifestyle, health-related physical fitness will be input variables, while frequency, duration, and intensity of exercise prescription will be output variables. We formulate the prescription learning process as a machine learning classification task. Explainable machine learning models such as logistics regression, support vector machine, decision tree, random forest, k-nearest neighbor, and naive Bayes classifiers will be utilized. Specifically, in the logistics regression machine learning model, the estimated values of coefficients and their standard deviations, *P*-values, and 95% confidence intervals, will provide us with the interpretability. The process of feature selection and kernels when using support vector machine may reveal the model interpretability (55). Figure presentation of trees and importance ranking of features for decision tree and random forest can lead to good explanations (56). In k-nearest neighbor algorithm, showing the k-nearest neighbors might also be explainable (57). As for Naive Bayes, it can be interpreted on the modular level and the conditional probability, then thus it will be very clear for us to understand how much each feature contributes toward a certain class prediction (58). Generally, these machine learning models may all have good potential for interpretability.

Some deep learning models will also be employed to evaluate the classification performance (accuracy, precision, recall, F-1 score, area under curve) in fivefold cross-validations, comparing them with the above-mentioned explainable machine learning models. Explanations of deep neural networks can be challenging (59), and hence to ensure that our deep learning models (convolutional neural networks, eXtreme gradient boosting, multilayer perceptron, deep residual network, DeepGBM) are more interpretable, an explainability tool named SHapley Additive exPlanations (SHAP), (60) will also be included. Recent advances in interpretability study for deep learning models have demonstrated the explainable potential for such models utilizing SHAP. For example, Zhao et al. proposed a novel SHAP scores computing algorithm for convolutional neural networks in classification (61). Meng et al. developed an integrated framework with better interpretability based on SHAP and eXtreme gradient boosting (62).

Since the intervention duration will be 2 years, there might be a great chance of loss-to-follow-up. Therefore, we set our sample size as 600 instead of 580, to cope with a higher loss rate or lower effectiveness rate than our initial estimations. If the final sample size for machine learning modeling still fails to reach the minimum bound (18), we will employ some few-shot learning algorithms (63) in such small size machine learning task to deal with this potential problem.

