**FIGURE 1 F1:**
[figure not shown]
The timeline of this study.

From 1 January 2023 to 31 December 2024, we will train our exercise prescription doctors in the training program for clinical exercise physiologist (CEP). This training program is jointly supported by American College of Sports Medicine (ACSM) and Chinese Association of Sports Medicine (CASM). Candidates who are admitted to this training program should either hold a bachelor’s degree (or above) in medicine/public health or have at least 3-year professional clinical experience in healthcare. Additionally, candidates are supposed to have a vast knowledge of physical education and sports training as well. In this training program, candidates need to complete reading materials, online courses, offline tutorials, practice, and examinations. The offline training activities will take place at Zhuhai, China, where a certificated training base of ACSM-CASM CEP programs locates on. After completion of all modules, our exercise prescription doctors will be certificated jointly by ACSM and CASM as CEP. From 1 January 2025 to 31 December 2026, we will recruit 600 participants who are PLWC (in Stage I) or cancer survivors (from Stage I) for this study. The baseline characteristics including demographics, cancer-related information, exercise habits and lifestyle, health-related physical fitness, and CVD-related items will be collected based on physical examination or biomedical testing, where necessary. Then the exercise prescription doctors certificated by ACSM-CASM will recommend exercise prescription to each participant based on the abovementioned variables. During the 2-year exercise intervention period, we will monitor each participant’s completion status through wearable devices, which can record one’s physical activity every day. Additionally, our health management team will keep track of participants every week to ensure their adherence. We will undertake the follow-up study between 1 January 2027 and 31 December 2028, re-examining CVD-related items for all participants. Finally, effective exercise prescription will be assessed based on the changes in CVD-related items from the baseline to the follow-up, and interpretable machine learning models will be adopted in effective exercise prescription. The intelligent exercise prescription recommendation system will be developed based on some machine learning models with both good interpretability and high performance.

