### 2.3 The sample size

We will recruit 600 participants for this study. Generally, the minimum sample size for machine learning modeling is 200 (18). We estimate the loss rate in the follow-up is 47% according to a finding that 53% cancer survivors do not follow the recommended physical activity guidelines (19). We infer that 65% of exercise prescriptions will be assessed as effective for cardio-oncology preventive care after the follow-up and used for machine learning modeling. This assumed value is based on the effectiveness rate of exercise prescriptions in reducing the risk of cardiovascular events among cancer patients (20). Therefore, at least 200÷65%÷53%=580.55 participants are needed. As a result, we decide to recruit 600 participants in the baseline to ensure the guarantee the minimum sample size for machine learning modeling at last.

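### The 'effective' label ignores recorded completion, so retained participants who did not perform the dose as prescribed can enter the training set as evidence for it

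*Protocol article*

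**What the plan says.** The article gives the rule for an effective prescription in three places, each time by change in cardiovascular items alone:

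- Section 2.1 (text after Figure 1): "effective exercise prescription will be assessed based on the changes in CVD-related items from the baseline to the follow-up".
- Section 2.4: "CVD-related items are used to evaluate the effectiveness of exercise prescriptions after comparing them with the follow-up data".
- Section 2.6: "Effective exercise prescriptions will be selected based on pre- and post-intervention data analysis of CVD-related items", with the one worked example that "if the blood pressure variability decreases or at least does not increase, the exercise prescription can be considered effective".

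Section 2.6 then fixes the modelling set, "We will employ interpretable machine learning models to the learnings on exercise prescription recommendations for all effective prescriptions", and the target, "frequency, duration, and intensity of exercise prescription will be output variables". The inputs are demographics, cancer information, habits and lifestyle, and physical fitness.

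Adherence data are planned. Section 2.5 says "During the 2-year exercise intervention period, wearable devices will be applied to monitor each" participant's completion status, and section 2.1 says activity is recorded daily. The stated uses are monitoring and weekly adherence support.

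Section 2.3 sets a 47% loss rate, and bases it on a finding that "53% cancer survivors do not follow the recommended physical activity guidelines".

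**The concern.** Every group of variables in the article has a role in the analysis except completion. The cardiovascular items make the label, four baseline groups are the inputs, and the prescribed dose is the output. A participant who returns for re-examination and whose blood pressure variability has not risen is labelled as a success for the dose on paper, whatever was actually done. The worked example can be met without exercising.

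Nothing in the article removes such a participant. Section 2.1 plans to re-examine everyone. In section 2.5 the deposit is returned after follow-up and the free equipment goes to those who stay in contact; neither is tied to completing the prescription. Section 2.3 comes closest to addressing the matter, because it derives loss from non-adherence, but it states no exclusion.

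What is at stake is the study's main product. The system is to recommend a dose and explain why (section 2.7). Where the dose was not performed as prescribed, the cardiovascular result says little about that dose, and any real relation between dose and response is diluted.

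**Working it through.** **The plan's own figure.** Section 2.3 needs 200 modelling cases, with 65% of prescriptions effective and 53% of participants retained: 200 / 0.65 / 0.53 = 580.55. This reproduces. With 600 recruited, 600 × 0.53 = 318 are retained and 318 × 0.65 = 206.7 are labelled effective.

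**Share of effective labels held by non-adherers.** Let q be the non-adherent share among retained participants, and let eN and eA be the proportions of non-adherers and adherers who meet the rule.

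Share = q·eN / [q·eN + (1 − q)·eA]

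The number retained cancels, so the share does not depend on the 47% loss as such. It depends on loss only through q.

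Inputs:

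- eA = 0.65. This is section 2.3's overall effectiveness rate, applied here to adherers (assumption).
- eN = 0.50 (assumption; the documents give none).
- q is not given in the documents. The values 20% and 30% are assumptions. The value 53% is the guideline finding cited in section 2.3, used as a high case.

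| q | q·eN | (1 − q)·eA | Share | Count among 318 retained |
|---|---|---|---|---|
| 0 (all non-adherers lost) | 0 | 0.650 | 0% | 0 of 207 |
| 0.20 | 0.100 | 0.520 | 0.100/0.620 = 16% | 32 of 197 |
| 0.30 | 0.150 | 0.455 | 0.150/0.605 = 25% | 48 of 192 |
| 0.53 | 0.265 | 0.3055 | 0.265/0.5705 = 46% | 84 of 181 |

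If non-adherers meet the rule as often as adherers (eN = 0.65), the share equals q: about 41, 62 or 110 of 207.

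**Cost of a hard completion threshold.** If only adherent and effective cases were kept, 318 × (1 − q) × 0.65 would leave 165 at q = 0.20, 145 at 0.30 and 97 at 0.53, all below the minimum of 200. Recruitment to restore 200 would be 580.55 / (1 − q): 726, 830 or 1,236, against 600 planned. This holds if the threshold comes on top of the 47% loss. If the 47% was already meant to cover non-adherers, no increase follows.

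**The case against.** **The 53% may not apply.** It describes cancer survivors in general against activity guidelines. The enrolled participants must be interested in exercise and willing to wear a device (section 2.2.1), and they are tracked weekly with incentives (section 2.5). This stands. A reader might infer that nearly half of the effective labels belong to doses never performed. The documents do not support that: they give no adherence rate for retained participants, they expect heavy loss, and falling short of a prescription can mean partial completion rather than none.

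**Section 2.3 may intend non-adherers to drop out.** Deriving loss from non-adherence points that way, and if all were lost the share would be zero. But no rule says so, and not adhering is a different event from not returning. This is a reason to reconcile the sections.

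**An article condenses.** A completion cut-off or the handling of missing wear time could well sit in a fuller document. The article does, however, state the effectiveness rule three times and allot the roles of the variables. The rule as stated is what is at issue.

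**A prescription can be judged as issued, followed or not.** That is a legitimate view where assigned groups are compared. Here everyone receives a prescription, there is no comparator, and individual cases are selected on their own outcome, so the argument does not carry over.

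**Adherence is not the only weakness of the label.** This also stands. If 50% met the rule without any exercise effect, then 0.50 / 0.65 = 77% of adherers' labels would be expected on that basis too. Using completion data leaves this untouched.

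**Conclusion.** The concern holds in this form: under the stated rule, retained participants who did not perform the dose as prescribed can enter the training set as evidence for it, although the data to tell them apart are being collected. That conclusion rests on the text alone.

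The size does not. With the assumed 50% and 65% rates, the affected share runs from 0% if all non-adherers are lost, through 16% and 25% at 20% and 30% non-adherence, to 46% at 53%. The top of that range is a high case and should not be quoted as the expected figure. The plan should be changed, and the change can be made in the analysis.

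**What to change.** - **Section 2.6:** keep all retained effective cases in the main modelling set, and model the wearable-recorded delivered dose (frequency, duration, intensity) as an output alongside the prescribed dose. It should not be a predictor, because it is unknown when the system makes a recommendation.
- **Sensitivity analysis:** repeat the modelling in prescriptions that meet a completion level fixed before the follow-up data are seen.
- **Section 2.3:** say whether the 47% covers non-adherence, loss to follow-up or both, and align sections 2.1, 2.3, 2.4 and 2.6 with the answer.

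The data are already planned, so the main change needs no new measurement and loses no cases. The costs are as follows. Missing wearable data must be handled. The completer analysis selects more motivated participants and may fall below 200 cases (about 165 at 20% non-adherence), so it should not replace the main set. Neither step supplies the missing comparator.

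### Training only on prescriptions judged effective, with the prescription as the output, mixes effectiveness with prescribing frequency, so a common but less effective prescription can be recommended

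*Protocol article*

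**What the plan says.** Section 2.6 of the protocol article sets out two steps. The first is a filter on outcome: "Effective exercise prescriptions will be selected based on pre- and post-intervention data analysis of CVD-related items". The only worked example of the rule is that "if the blood pressure variability decreases or at least does not increase, the exercise prescription can be considered effective". The second step fits models to what passes the filter: "We will employ interpretable machine learning models to the learnings on exercise prescription recommendations for all effective prescriptions".

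The same section fixes the learning task. "Demographics, cancer-related information, exercise habits and lifestyle, health-related physical fitness will be input variables", and "frequency, duration, and intensity of exercise prescription will be output variables". It adds: "We formulate the prescription learning process as a machine learning classification task". Cardiovascular items are neither inputs nor outputs; they serve only to select records. Section 2.5 has the prescribers work from the same four baseline domains, and every participant receives a prescription, so there is no comparator.

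Section 2.3 confirms that the filter is meant literally. It expects that "65% of exercise prescriptions will be assessed as effective for cardio-oncology preventive care after the follow-up and used for machine learning modeling", and divides by that 65% to reach the sample size. Section 2.6 compares models by accuracy, precision, recall, F-1 and AUC in fivefold cross-validation, and section 2.7 builds the system from models chosen on performance and interpretability.

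**The concern.** The system is meant to support preventive care by recommending effective prescriptions. To say that one prescription is more effective than another for a given type of patient, the data must show how often each succeeded and how often each failed. Under section 2.6 every training record is a success, so the effectiveness label is constant and the chance of success given prescription and patient cannot be estimated. What remains is the mix of prescriptions among successes, which depends on both prescribing frequency and effectiveness.

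The consequence is practical. A frequently used prescription can dominate the training set while working less well than a rarer one, and the model would recommend it. The planned metrics would not reveal this, because they score whether the model names the prescription that the prescriber gave.

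**Working it through.** **Inputs.** From section 2.3: 600 recruited, 53% retained (the factor used in the plan's calculation), 65% judged effective, and a modelling minimum of 200. Prescription splits and prescription-specific effectiveness rates are not in the document; those below are assumptions for illustration.

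**The plan's figure.** 200 ÷ 0.65 ÷ 0.53 = 580.55, as stated. It reproduces only if the other 35% are removed before modelling, which confirms effective-only training.

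**Records kept and dropped.**
- Completers: 600 × 0.53 = 318
- Used for training: 318 × 0.65 = 206.7, about 207
- Dropped: 318 × 0.35 = 111.3, about 111

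**What the classifier estimates.** For prescription A and patient type X, Bayes' rule gives

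P(A | X, effective) = P(A | X) × P(effective | A, X) ÷ P(effective | X).

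The first factor is prescribing frequency and the second is effectiveness. Only their product is visible in the training set.

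**They cannot be separated.** Suppose the training set is 70% A and 30% B, with 65% effective overall. Effective records are then 0.70 × 0.65 = 0.455 of all completers for A and 0.30 × 0.65 = 0.195 for B. Dividing by the share prescribed gives:

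| A prescribed to | A effective | B effective |
|---|---|---|
| 50% | 91% | 39% |
| 60% | 76% | 49% |
| 70% | 65% | 65% |
| 80% | 57% | 97.5% |

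The training data are identical in all four rows, yet the ranking of A and B reverses.

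**When the less effective option wins.** Assume A works in 55% and B in 85%, and that the system recommends the most probable class.
- 80/20 split: A contributes 0.80 × 0.55 = 0.44 and B 0.20 × 0.85 = 0.17. A's share is 0.44 ÷ 0.61 = 72%, so A is recommended. Overall effectiveness here is 61%, slightly below the plan's 65%.
- The same split set to exactly 65% overall (A 60%, B 85%): 0.48 ÷ 0.65 = 73.8% for A.
- 60/40 split, 55% vs 85%: A contributes 0.33 and B 0.34 (67% effective overall), so B is just favoured.
- Break-even at 55% vs 85%: B wins once it is given to more than 0.55 ÷ (0.55 + 0.85) = 39% of such patients.

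**Limit on the filter.** At 65% overall effectiveness, the filter can raise a prescription's share by at most 1 ÷ 0.65 = 1.54-fold, reached only if that prescription always works.

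**Simulation.** 318 completers, 5,000 runs, two options, one patient type, and prescription unrelated to prognosis:
- 80/20 split, 60% vs 85%: effective-only training favoured A in 100% of runs.
- 70/30 split, 50% vs 100%: it favoured A in 86% of runs.
- Comparing success rates in all completers ranked B higher in 100% of runs in both settings.

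The last result shows that the dropped records carry the missing information. It does not show that confounding would be absent in the real cohort.

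**The case against.** A reader might infer that the system learns only prescribing habit, or that a perfectly accurate model would merely copy current practice. The document does not support that. The filter carries effectiveness information, and the 60/40 case shows it moving the recommendation to the better option. Where two prescriptions both succeed in the same type of patient, perfect accuracy is not attainable: in the 80/20 illustration, always naming A would be right 72% of the time. Nor does anything in the document show that habit usually dominates, since no prescribing split is given.

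The aim can also be read more modestly. The article cites the shortage of medical resources, and its conclusion speaks of learning the prescribing process. The prescribers are certified specially for the study, so reproducing their successful decisions could have value. Section 3 calls internal cross-validation an initial choice and defers a quasi-experimental external validation to another study, so accuracy and AUC are not offered as the final test.

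These points narrow the claim but do not remove it. Sections 2.1 and 2.6 tie the system to effective prescriptions, so the aim is at best ambiguous. The external validation is to follow real use of the system and leaves the training target unchanged. Section 3 does not list this problem among its limitations.

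An outcome model has weaknesses too. Prescriptions are assigned from the same characteristics used as inputs, there is no comparator, and about 318 completers would be spread over many combinations of frequency, duration and intensity. That objection stands and belongs in the plan.

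**Conclusion.** The point holds in this form: the training rule in section 2.6 cannot separate effectiveness from prescribing frequency, and it can therefore recommend a common but less effective prescription. The article itself fixes the training set, the output and the sample size on this basis, so this is not a detail left to a fuller plan.

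About 111 of 318 expected completers, the only records showing where a prescription did not work, are discarded. That figure rests on the plan's 53% and 65%. How often a recommendation would be wrong cannot be stated, because it depends on prescribing splits and effectiveness rates that the document does not give. The 72% figure is an illustration under assumed rates and a most-probable-class rule, which section 2.7 does not specify. The planned performance metrics would measure agreement with the study's prescribers and could not detect the error.

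**What to change.** Rewrite section 2.6 as follows.

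- Keep all followed-up participants in the primary model.
- Use the follow-up cardiovascular item or items as the outcome. Take prescription, baseline characteristics and baseline cardiovascular items as predictors, with a small number of pre-specified or penalised prescription-by-feature interactions.
- Restrict recommendations to prescriptions actually observed in similar patients.
- Evaluate them by a cross-validated estimate of the outcome under the recommendations compared with the outcome as prescribed.
- Keep the present classifier as a secondary, descriptive analysis of prescribing.
- State the limits: reliance on measured confounders, no comparator, and limited overlap and precision with about 318 completers over many prescription combinations.

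If the outcome model is not adopted, restate the aim and conclusions as reproducing certified prescribers' decisions among patients who did not worsen, and make no claim that the system identifies effective prescriptions.

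The cost is plan wording and additional analysis. Cardiovascular items are already to be measured at baseline and follow-up for all participants, so neither route needs more recruitment or data, and the intervention and follow-up are unchanged.

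### The three prescription outputs are ordered quantities, but the listed performance measures ignore how far a recommendation lies from the prescribed level

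*Protocol article*

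**What the plan says.** Section 2.5 (Interventional methods) defines the components of a prescription: "Frequency is the number of times of exercise per week", and "duration is the length of time in total, and intensity is decided to be high, moderate, or low". It adds that the three can be combined on a MET-h/week scale.

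Section 2.6 (Data analysis and interpretable learning) makes these the targets of the model: "frequency, duration, and intensity of exercise prescription will be output variables". It sets the task type: "We formulate the prescription learning process as a machine learning classification task". The explainable learners are given as examples: "logistics regression, support vector machine, decision tree, random forest, k-nearest neighbor, and naive Bayes classifiers will be utilized". These are compared with deep learning models on "classification performance (accuracy, precision, recall, F-1 score, area under curve) in fivefold cross-validations".

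Sections 2.7 and 3 say that the system will be built on models that balance performance with interpretability. Neither section names an ordinal learner, a regression for a numeric target, or a distance-weighted error measure.

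**The concern.** A count, a length of time and a three-step scale all have an order. For a recommender of exercise dose, the natural question is how far the recommendation falls from what the certified prescriber wrote, not only whether it matches. The listed measures answer the second question.

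The performance comparison feeds the choice of model for the deployed system. If it does not score distance, a model that often misses by the full width of the scale can rank level with, or above, one whose misses are nearly all adjacent. The modelling set is small, so any order information left unused is also a cost, although the working shows that this part is modest.

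**Working it through.** **1. Size of the modelling set.** Inputs from Section 2.3: minimum 200, effectiveness 65%, retention 53%, recruitment 600.
- The plan's own figure: 200 ÷ 0.65 ÷ 0.53 = 580.55, which reproduces.
- Expected records from 600 recruited: 600 × 0.53 × 0.65 = 206.7.
- One fivefold training set: 0.8 × 206.7 ≈ 165.

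**2. What the scoring can see.** Take 200 records with true intensity low/moderate/high = 67/67/66 (an assumed even split) and 40 errors. Quadratic-weighted kappa = 1 − (weighted observed disagreement) ÷ (weighted expected disagreement). The weight is 0.25 for a one-level error and 1 for a two-level error.

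| Pattern of the 40 errors | Accuracy | Mean absolute level error | Weighted kappa |
|---|---|---|---|
| A. 20 low and 20 high predicted as moderate | 160/200 = 0.80 | 40/200 = 0.20 | 1 − 10/56.50 = 0.82 |
| B. 10 each: low→moderate, moderate→low, moderate→high, high→moderate | 0.80 | 0.20 | 1 − 10/66.50 = 0.85 |
| C. 20 low→high and 20 high→low | 0.80 | 80/200 = 0.40 | 1 − 40/66.50 = 0.40 |

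B and C have the same predicted totals (67/67/66), so precision equals recall in each class and F-1 equals both.
- B, average over classes: (57/67 + 47/67 + 56/66)/3 = 0.80.
- C, average over classes: (47/67 + 67/67 + 46/66)/3 = 0.80.

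The four count-based measures, averaged over classes, therefore agree to two decimals for two recommenders with a twofold difference in distance. In A the average precision is (47/47 + 67/107 + 46/46)/3 = 0.88. It differs because it depends on which class receives the errors, not on how far off they are. AUC needs predicted probabilities, so this table does not fix it. It measures separation between classes and has no distance weight.

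**3. Accuracy can prefer the worse dose error.** This is a simulation with 165 training records, 17 inputs (6 informative), a proportional-odds truth and 30 replicates. The same fitted ordinal model is read out as the most probable class or as the median class. The 5- and 7-level cases are assumptions.

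| Levels | Accuracy, most probable vs median | Two or more levels off, most probable vs median |
|---|---|---|
| 3 | 0.465 vs 0.454 | 12.4% vs 7.2% |
| 5 | 0.297 vs 0.277 | 34.3% vs 28.5% |
| 7 | 0.220 vs 0.202 | 48.9% vs 44.8% |

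Accuracy favours the first readout every time, although it makes more large errors.

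**4. Separating the model from the readout.** This is a simulation of the same kind, with assumed log-odds of 0.4 per SD. It shows mean absolute error in levels.

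| Levels | Nominal, most probable | Nominal, median | Ordinal, median | Share of gain from readout |
|---|---|---|---|---|
| 3 | 0.69 | 0.65 | 0.63 | 0.04/0.06 = 67% |
| 5 | 1.31 | 1.16 | 1.10 | 0.15/0.21 = 71% |
| 7 | 1.85 | 1.63 | 1.54 | 0.22/0.31 = 71% |

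With the median rule held fixed, ordinal modelling lowers the error by 0.02/0.65 = 3%, 0.06/1.16 = 5% and 0.09/1.63 = 6%. Other runs, including some under the most-probable-class rule, agree, and allowing for rounding the range is roughly 2 to 6%.

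**5. Parameter count, logistic regression only.** Table 1 has 4 + 4 + 5 + 4 = 17 input rows, each counted here as one term. For three-level intensity, the only output with a stated number of levels, a nominal model needs (3 − 1) × (17 + 1) = 36 parameters. A proportional-odds model needs 17 + 2 = 19.

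**The case against.** The strongest reply is that the plan is internally consistent: a classification task, classifiers and classification measures. It contains no contradiction or false statement. Several further points stand.

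- A reader might infer that the plan treats the outputs as unordered classes. The article does not say so. The learner list is introduced as examples, and an ordinal form of logistic regression is not excluded. The absence of order is inferred from the task and the measures. How frequency and duration are cut into classes is a detail that a condensed article may leave to a fuller document.
- A reader might illustrate the problem with 155 minutes scored as wrong against 150. That presumes a very fine cut of duration that is stated nowhere, and under ordinary bins the two would usually share a class. Nor can 375 against 150 minutes serve as a gross error. Those totals correspond to the two sample prescriptions in Section 2.5 (5 × 75 = 375, and 150), which that section itself calls equivalent. Whether that equivalence holds is a separate matter.
- A reader might infer that nominal modelling wastes a large share of a scarce sample. Step 4 does not support this. The parameter count also applies to one learner among many.
- Performance is not the only criterion. Interpretability counts too, and external validation is planned in another study.
- Component-wise distance can penalise prescriptions that Section 2.5 regards as equal on the MET scale. This is a fair caution when reading the new measures, but the listed measures share the problem, since they also compare component by component.

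None of this removes the scoring point. Even with an ordinal learner, the listed measures would not weight an error by its distance.

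**Conclusion.** The concern holds as a point about scoring. By the article's own definitions the outputs are ordered, and none of the listed measures weights an error by distance. In the worked example, near misses and low-high swaps both score 0.80 on accuracy, while mean absolute level error doubles from 0.20 to 0.40 and weighted kappa falls from 0.82–0.85 (depending on the marginals) to 0.40. That result needs no modelling assumption beyond the illustrative split and error count.

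The modelling part is secondary. The 2 to 6% gain rests on assumed effect sizes, on assumed level counts for all but intensity, and on a proportional-odds truth that favours the ordinal fit. Ordinal and regression learners therefore belong among the candidates and need not replace the listed classifiers. That a widely missing model would in fact be chosen is a risk, not something that the documents show.

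**What to change.** In Section 2.6:

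- Add distance-aware measures as main performance criteria in the fivefold cross-validation: quadratic-weighted kappa and mean absolute error for intensity and frequency, and mean absolute error in time units for duration.
- Keep accuracy, precision, recall, F-1 and AUC alongside.
- Include ordinal logistic regression for intensity and frequency, and a regression version for duration, among the candidate learners.
- Use a readout that respects distance, such as the predicted median.

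The cost is analysis wording, slightly more programming and a check of the proportional-odds assumption. Recruitment, data collection and the intervention do not change, and no view is taken on which exercise dose is right.
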